# Efficacy of one-stage cartilage repair using allogeneic mesenchymal stromal cells and autologous chondron transplantation (IMPACT) compared to nonsurgical treatment for focal articular cartilage lesions of the knee: study protocol for a crossover randomized controlled trial

**DOI:** 10.1186/s13063-020-04771-8

**Published:** 2020-10-09

**Keywords:** Articular cartilage defect, Chondrocytes, Chondrons, Mesenchymal stromal cells (MSC), Surgery, Knee, Randomized controlled trial (RCT), Crossover design, Advanced therapy medicinal product (ATMP)

## Abstract

**Background:**

Articular cartilage defects in the knee have poor intrinsic healing capacity and may lead to functional disability and osteoarthritis (OA). “Instant MSC Product accompanying Autologous Chondron Transplantation” (IMPACT) combines rapidly isolated recycled autologous chondrons with allogeneic MSCs in a one-stage surgery. IMPACT was successfully executed in a first-in-man investigator-driven phase I/II clinical trial in 35 patients. The purpose of this study is to compare the efficacy of IMPACT to nonsurgical treatment for the treatment of large (2–8 cm^2^) articular cartilage defects in the knee.

**Methods:**

Sixty patients will be randomized to receive nonsurgical care or IMPACT. After 9 months of nonsurgical care, patients in the control group are allowed to receive IMPACT surgery. The Knee Injury and Osteoarthritis Outcome Score (KOOS), pain (numeric rating scale, NRS), and EuroQol five dimensions five levels (EQ5D-5 L) will be used to compare outcomes at baseline and 3, 6, 9, 12, and 18 months after inclusion. Cartilage formation will be assessed at baseline, and 6 and 18 months after inclusion using MRI. An independent rheumatologist will monitor the onset of a potential inflammatory response. (Severe) adverse events will be recorded. Lastly, the difference between IMPACT and nonsurgical care in terms of societal costs will be assessed by monitoring healthcare resource use and productivity losses during the study period. A health economic model will be developed to estimate the incremental cost-effectiveness ratio of IMPACT vs. nonsurgical treatment in terms of costs per quality adjusted life year over a 5-year time horizon.

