IMPACT surgery [21, 22] consists of a mini-arthrotomy, during which the cartilage defect is debrided and stable borders are created. The debrided cartilage tissue is transported to the Cell Therapy Facility, where chondrons are isolated from the tissue using a rapid digestion protocol; minced cartilage is digested in 40 min in Liberase MNP-S GMP Grade (Roche, Mannheim, Germany). The autologous chondron-suspension is run over a 100-μm strainer (Corning Inc., New York, USA) to remove the undigested cartilage matrix. The chondrons are washed twice to remove the enzyme and counted using 3% acetic acid with methylene blue (STEMCELL Technologies Germany GmbH, Köln, Germany). Allogeneic cryopreserved MSC are thawed and the chondrons and MSCs are mixed at a 10:90 ratio in the fibrinogen component of Tisseel®. The fibrinogen and thrombin component of Tisseel® are mixed upon application, which causes the product to gelate. Two million cells per milliliter are implanted in the defect. The rehabilitation protocol we use is equal to that after ACI. Briefly, during rehabilitation, patients are allowed 10% weight-bearing the first 3 weeks, after which the load is increased gradually up to 50% at 6 weeks and 100% at 8 to 12 weeks. From 5 months onward, the rehabilitation protocol aims at improving coordination, increasing muscle strength, and becoming functional in moderately intensive activities. Patients can return to low-impact sports after 9 months and to high-impact sports at the earliest after 12 months. Patients treated for cartilage defects in the trochlea are allowed weight-bearing in the first 6 weeks after surgery but will use an extension brace in order to limit the flexion while weight-bearing.

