
### Participant timeline {13}

Table 1 shows the participant timeline.

**Table 1 Tab1:** Participant timeline

**Outpatient Clinic:** Screening (MRI) Study information provided in writing	
**Baseline visit:** Informed consent Baseline study MRI Randomization Baseline PROMs	
Group A: IMPACT	Group B: Control (nonsurgical)
**Preoperative screening** Anti-HLA antibodies	**3 months after inclusion** PROMs Check-up study physician (by telephone)
**Surgery/1 day postoperative** Blood chemistry (CRP, ESR, Leucocytes) Visit physical therapist Check-up rheumatologist Check-up study physician	**6 months after inclusion** PROMs Check-up study physician MRI
**1 week postoperative** Blood chemistry (CRP, ESR, Leucocytes) Check-up rheumatologist Check-up study physician	**9 months after inclusion** PROMs
**4 weeks postoperative** Blood chemistry (CRP, ESR, Leucocytes, anti-HLA antibodies) Check-up rheumatologist Check-up study physician	In case of cross-over to IMPACT: follow group A In case nonsurgical treatment is continued: **12 months after inclusion:** PROMs
**3 months postoperative** Check-up study physician (by telephone) PROMs	**18 months after inclusion:** PROMs MRI
**6 months postoperative** Check-up study physician PROMs MRI	
**9 months postoperative** PROMs	
**12 months postoperative** Check-up study physician PROMs	
**18 months postoperative** Check-up study physician PROMs MRI	

*CRP* C-reactive protein, *ESR* erythrocyte sedimentation rat, *HLA* human leukocyte antigens, *IMPACT* Instant MSC Product accompanying Autologous Chondron Transplantation, *MRI* magnetic resonance imaging; *PROMs* patient-reported outcome measures

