## Data collection and management

### Plans for assessment and collection of outcomes {18a}

Data will be derived from electronic patient records and collected with an electronic Case Report Form (eCRF) using Castor EDC (Good Clinical Practice (GCP) Compliant) [26]. Patients will use an online survey (OnlinePROMS, InterActive Studios, Rosmalen, the Netherlands) to answer questionnaires. Laboratory tests are performed by the central diagnostic laboratory and MRIs will be made at the Department of Radiology of the UMC Utrecht. All radiographic data acquired during the study will be anonymized and saved in a study folder on our protected research server. Only the study team has access to this specific study folder. For the cost-effectiveness analysis, the resources required for the different procedures (i.e., IMPACT or nonsurgical treatment), as well as for the IMPACT product that is used (materials, operation theater, etc.), and the duration of the accompanying hospitalization will be derived from the electronic patient records. In addition, the results of the iMTA Medical Consumption Questionnaire will be used to collect data on resource use (including physiotherapist visits, home care, and medication use) and the results of the iMTA Productivity cost questionnaire will be used to collect data on productivity losses [27]. All resource use will be multiplied with cost prizes, which will be obtained from the Dutch Healthcare Authority [28], from UMC Utrecht hospital tariffs or from the Dutch manual for performing health economic evaluations [29], to calculate total societal costs. These costs will be combined with the QoL outcome measures (EQ-5D-5L), to calculate the incremental cost-effectiveness ratio of IMPACT compared to nonsurgical therapy in terms of cost per QALY over a 5-year time horizon.

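### Table 1 schedules no EQ-5D-5L between baseline and 3 months after surgery, so a postoperative utility loss would go unobserved and IMPACT's QALYs are likely overstated against nonsurgical care if those two points are simply joined

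*Protocol article*

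**What the plan says.** The abstract of the protocol article states that KOOS, pain and the EQ-5D-5L "will be used to compare outcomes at baseline and 3, 6, 9, 12, and 18 months after inclusion". Table 1 (Participant timeline) sets out the IMPACT arm by time since surgery. The 4-week entry reads "Blood chemistry (CRP, ESR, Leucocytes, anti-HLA antibodies) Check-up rheumatologist Check-up study physician", and the 1-day and 1-week entries likewise list no patient-reported outcomes. The first postoperative entry that does is at 3 months: "Check-up study physician (by telephone) PROMs". Control patients who cross over are to follow the IMPACT schedule.

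The intervention description allows 10% loading for the first 3 weeks, after which "the load is increased gradually up to 50% at 6 weeks and 100% at 8 to 12 weeks". There is an exception: "Patients treated for cartilage defects in the trochlea are allowed weight-bearing in the first 6 weeks after surgery", with an extension brace.

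On the economic analysis, the section on outcome collection says "These costs will be combined with the QoL outcome measures (EQ-5D-5L), to calculate the incremental cost-effectiveness ratio of IMPACT compared to nonsurgical therapy", over a 5-year horizon. The Outcomes section defines two comparisons: scenario I, IMPACT versus nonsurgical treatment, and scenario II, IMPACT versus delayed surgery. It takes the IMPACT extrapolation from unpublished phase I/II results. One-way and probabilistic sensitivity analyses are planned. The article does not say how utilities between visits become QALYs, and it neither states nor rules out a utility decrement for surgery.

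**The concern.** On Table 1's clock the restricted-loading period lies wholly between two utility measurements. Any health loss that surgery causes in those weeks is therefore not observed in the trial. A later analysis plan can choose an interpolation rule or assume a decrement, but it cannot recover measurements that were never taken.

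In scenario I only the surgical strategy goes through this recovery, so a missed loss would favour IMPACT. It would also not shrink with more patients. The cost side has no matching gap: resource use and productivity losses are monitored throughout the study period, so early recovery counts in the numerator of the ratio while its health effect may be absent from the denominator. The cost-effectiveness ratio is a stated objective. The primary KOOS comparison is not affected by this point.

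**Working it through.** The article gives no QALY figure or ratio to reproduce, and its sample-size calculation does not enter here.

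**Inputs from the article.** Utility at baseline and 3 months (13.04 weeks, at 52.18 weeks per year); loading at 10% to week 3 and 100% at week 8 to 12; 5-year horizon.

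**Assumptions (not in the article).** Utility falls by D at surgery, stays there to week 3, then rises in a straight line to its 3-month value at week T = 8 or 12. The 3-month value differs from baseline by d = −0.10, 0 or +0.10. D runs from 0 to 0.4. The analysis joins baseline to 3 months by a straight line and adds no surgical decrement.

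**Step 1: QALYs missed per IMPACT patient.** Area under the straight line minus area under the assumed path:

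E = [6.52d + 3D + (D − d)(T − 3)/2 − d(13.04 − T)] / 52.18

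- T = 8: E = (5.5D − 1.02d)/52.18
- T = 12: E = (7.5D + 0.98d)/52.18

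| Dip D | d = 0, T = 8 | d = 0, T = 12 | Range over T and d |
|---|---|---|---|
| 0 | 0 | 0 | −0.002 to 0.002 |
| 0.1 | 0.011 | 0.014 | 0.009 to 0.016 |
| 0.2 | 0.021 | 0.029 | 0.019 to 0.031 |
| 0.3 | 0.032 | 0.043 | 0.030 to 0.045 |
| 0.4 | 0.042 | 0.057 | 0.040 to 0.059 |

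**Step 2: effect on the scenario I ratio.** Let g be the lasting utility gain, reached linearly by 3 months and held to 5 years, undiscounted. The incremental QALYs computed without the dip are 4.75g + 0.125g = 4.875g. With costs fixed, the true ratio exceeds the computed one by the factor 4.875g/(4.875g − E).

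- g = 0.10: 0.4875/0.4675 = 1.04 for E = 0.02; 0.4875/0.4575 = 1.07 for E = 0.03.
- g = 0.05: 0.2438/0.2238 = 1.09 for E = 0.02; 0.2438/0.2138 = 1.14 for E = 0.03.

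This gives 4% to 14%. The outer corners are 0.4875/0.4775 = 1.02 (E = 0.01, g = 0.10) and 0.2438/0.1838 = 1.33 (E = 0.06, g = 0.05).

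**Step 3: the abstract's clock.** If the 3-month reading is taken from inclusion, it falls at postoperative week 11, 9, 7 or 5 when surgery follows inclusion by 2, 4, 6 or 8 weeks. The wait is not given; these values are assumptions. With T = 12 and d = 0, the shortfall seen at that reading is D(12 − week)/9. Straight lines from baseline to 3 to 6 months turn it into an area of 13.04 times that value, against a true loss of 7.5D. The share captured is about 19%, 57%, 96% and 135%. On this clock the error shrinks and can turn against IMPACT.

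**Step 4: what two early readings would recover.** With T = 12, d = 0 and readings at weeks 0, 1, 4 and 12 of 0, D, 8D/9 and 0 below baseline, the area is 0.5D + 2.83D + 3.56D = 6.89D, which is 6.89/7.5 = 92% of the loss. If recovery is complete by week 8, the week-4 shortfall is 0.8D and the next reading is at week 13.04. The area is then 0.5D + 2.7D + 3.62D = 6.82D against a true 5.5D, or 124%. Two readings remove most of the error, but the straight line after week 4 can over-correct if recovery is fast.

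**The case against.** A reader might infer that IMPACT's QALYs are overstated as a matter of fact. The article does not support that. It needs a material utility dip and a model that joins the two readings without a surgical decrement, and the article fixes neither. A model could carry an assumed decrement and vary it in the planned sensitivity analyses, and such detail is commonly left to a fuller plan. This objection stands, and it is why the conclusion is conditional. It does not close the gap, because such a decrement would have to be assumed or borrowed: the article names the phase I/II data only for the extrapolation.

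A reader might also infer that the whole recovery period goes unmeasured in every patient. That follows from Table 1 but not from the abstract, which counts from inclusion (Step 3). Patients with trochlear defects may bear weight in a brace, so the dip may differ by site. Loading is also not utility, and rehabilitation continues well after 3 months.

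A third inference is that every comparison is biased. In scenario II the delayed-surgery patients go through the same unmeasured recovery, so the error largely cancels.

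Finally, a larger distortion, 11% to 24%, can be produced with D = 0.3 and no benefit before month 6. That delays the benefit by assumption and so shrinks the denominator; it should not be the headline size.

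**Conclusion.** The gap is real on Table 1's schedule: no utility is collected between baseline and 3 months after surgery, although loading is restricted until 8 to 12 weeks for condylar defects. If utility dips and the two readings are joined, scenario I is likely to favour IMPACT by about 0.01 to 0.06 QALY per patient for a dip of 0.1 to 0.4, and by about nothing without a dip. For an error of 0.02 to 0.03 QALY and a lasting gain of 0.05 to 0.10, the ratio is understated by roughly 4% to 14%. The dip, its shape and the lasting gain are all assumptions. The effect is modest, but it is worth correcting because the missing data cannot be recovered later and the visits already exist.

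**What to change.** - **Collect.** Add the EQ-5D-5L at the existing 1-week and 4-week postoperative visits for every IMPACT recipient, crossovers included, and online at matching times in controls.
- **Analyse.** Use these values in the QALY calculation, on actual assessment dates. Given the possible over-correction in Step 4, let the sensitivity analyses vary the recovery path between week 4 and 3 months.
- **Patients already past these visits.** Enter the postoperative loss measured in later patients as a model input and vary it in the planned one-way and probabilistic analyses. Ten of 60 patients had been included by mid-May 2020, so most could still be measured.
- **Reconcile the clock.** State whether the 3- to 18-month questionnaires in the IMPACT arm run from inclusion (abstract) or from surgery (Table 1), and how the wait for surgery enters the QALYs.

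The cost is a short questionnaire twice, an amendment to Table 1 and slight patient burden. The ratio may come out slightly less favourable to IMPACT.

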### Objectives {7}

The current phase III randomized controlled trial explores the efficacy of IMPACT compared to nonsurgical care in 60 patients with large (2–8 cm^2^) articular cartilage defects of the knee. We allow patients in the nonsurgical group to cross-over to the IMPACT group after 9 months of nonsurgical care. Follow-up will be at least 18 months after IMPACT. The primary objective is to compare the Knee Injury and Osteoarthritis Outcome Score (KOOS) at 3, 6, and 9 months follow-up. The secondary objective of this study is to examine morphology and proteoglycan content of repair tissue 6 and 18 months after treatment. Safety endpoints will be determined by the number of (treatment-related) adverse events. In addition, the incremental cost-effectiveness ratio (ICER) of IMPACT vs. nonsurgical care and vs. delayed surgical intervention will be calculated. More specifically, the effect of IMPACT compared with nonsurgical care and delayed surgical intervention in terms of healthcare resource use, productivity losses, and accompanying costs during the study period will be determined and extrapolated to a 5-year time horizon.

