### Trial design {8}

In this phase III randomized controlled clinical trial, IMPACT is compared to nonsurgical treatment. The patient allocation ratio is 1:1. Patients in the nonsurgical group are allowed to cross over to the treatment group after 9 months follow-up.

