### Outcomes {12}

The primary outcome is the comparison in total KOOS between patients with cartilage defects that are treated with IMPACT and patients treated with standard care (nonsurgical treatment) until 9 months after randomization. Total KOOS is an average of the scores in the five subscales of KOOS [23]. Other outcomes of interest are outcomes in the five subscales of KOOS, pain (numeric rating scale, NRS), general health (EuroQol five dimensions five levels, EQ5D-5 L), and structural repair (MRI). After 9 months, patients in the nonsurgical group are allowed to undergo IMPACT surgery, this will be regarded as failed nonsurgical treatment, and the time of crossover will be recorded. Change from baseline assessed with the KOOS of the total group of patients treated with IMPACT at 3, 6, 9, 12 and 18 months after treatment will be evaluated (per protocol). The potential effect of time until surgical treatment will be assessed. Clinical safety will be determined by active tracing of the adverse event rate observed after IMPACT and nonsurgical therapy. Additionally, emergence of an immune response will be assessed by screening for anti-HLA antibodies in peripheral blood preoperatively and 4 weeks postoperatively. The HLA phenotype of MSC donors will be compared to newly formed anti-HLA antibodies. Societal costs will be assessed by monitoring the costs related to the IMPACT procedure and the accompanying rehabilitation period, as well as costs related to nonsurgical (or delayed) treatment. In this analysis, two scenarios will be compared: (I) IMPACT vs. nonsurgical treatment and (II) IMPACT vs. delayed surgical treatment. In the first scenario, it is assumed that patients randomized to nonsurgical treatment will not undergo IMPACT in the next 5 years, whereas the second scenario includes patients who were randomized to nonsurgical care and opt for IMPACT after 9 months follow-up. In both scenarios, costs of other healthcare-related resource use (including physiotherapy, home care, medication use, and costs related to adverse events), as well as costs attributable to health-related work leave (i.e., productivity losses), will be collected over a follow-up period of (at least) 9 months. For nonsurgical treatment, health outcomes (from the EQ-5D-5L) and costs within the first 9 months will be extrapolated to calculate costs/QALY over a 5-year time horizon. Similarly, health outcomes and costs for (delayed) IMPACT will also be extrapolated to a five-year time horizon, using results from the completed phase I/II study (unpublished results).

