## Statistical methods

### Statistical methods for primary and secondary outcomes {20a}

Data will be analyzed using IBM SPSS (version 15.0.0.2, Chicago, IL). Data from the primary objective (KOOS, EQ-5D-5L) will be presented as continuous variables. To compare between the two treatment groups, a mixed model analysis will be performed, with treatment group and assessment date of the PROMs (e.g., baseline, 3 months, 6 months) as fixed factors. Differences will be considered statistically significant for the fixed effect of treatment groups if *p* < 0.05 [30]. The 95% confidence interval of the fixed effect size will be used to assess whether treatment difference reaches the minimally clinical important difference.

T1rho-scores will be calculated from the biochemical MRI scans; differences in T1rho-scores will be compared between the time points *t* = 0 (at inclusion before IMPACT or nonsurgical treatment) and *t* = 6 and 18 months after inclusion or surgery. Differences will be compared using Student’s *t* test. The differences in T1rho-score will be tested for normality using Q–Q plots. *P* values less than 0.05 will be considered significant. We will calculate the ICERs of IMPACT vs. nonsurgical treatment and vs. delayed surgical treatment in terms of cost/QALY over a 5-year time horizon. The effect of uncertainty in input parameters on the ICERs will be calculated by means of one-way sensitivity analysis as well as probabilistic sensitivity analyses using Monte Carlo simulation.

All (S)AE(I)s will be summarized and recorded including the nature, date and time of onset, date of resolution, determination of seriousness, severity, action taken, outcome, and possible causality to study treatment. SAE data will be presented in a descriptive manner.

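### The PROM comparison announced at 12 and 18 months after inclusion has, on the control side, only patients who did not cross over; IMPACT-versus-nonsurgical contrasts should stop at 9 months

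*Protocol article*

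**What the plan says.** All references are to the protocol article.

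- **Abstract, Methods:** the three PROMs "will be used to compare outcomes at baseline and 3, 6, 9, 12, and 18 months after inclusion". The sentence follows directly on those describing randomisation and the option of surgery for controls after 9 months.
- **Trial design {8}:** "Patients in the nonsurgical group are allowed to cross over to the treatment group after 9 months follow-up".
- **Participant timeline {13}, Table 1:** after the 9-month control visit the path divides: "In case of cross-over to IMPACT: follow group A In case nonsurgical treatment is continued". The 12- and 18-month visits after inclusion, including the 18-month MRI, are listed only on the second branch. The group A schedule is timed from surgery.
- **Outcomes {12}:** of crossover, "this will be regarded as failed nonsurgical treatment, and the time of crossover will be recorded".
- **Objectives {7}:** "The primary objective is to compare the Knee Injury and Osteoarthritis Outcome Score (KOOS) at 3, 6, and 9 months follow-up". Outcomes {12} likewise ends the primary total-KOOS comparison at 9 months after randomisation. It names the KOOS subscales, pain, EQ-5D-5L and MRI as other outcomes without giving an end point for their comparison between arms.
- **Statistical methods {20a}:** the mixed model has treatment group and assessment date as fixed factors, with visits given only as examples. T1rho is compared by t test between baseline and "6 and 18 months after inclusion or surgery".
- **Section {20c}:** intention-to-treat is stated for the primary outcome.

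**The concern.** After month 9 the control arm is no longer complete as randomised. Patients who choose surgery leave the after-inclusion schedule, and the plan itself labels their departure a failure of the control treatment. Those who remain are likely to be the ones doing well enough to decline surgery. Comparing all IMPACT patients with them at 12 or 18 months sets a randomised group against a self-selected one, and the likely error makes nonsurgical care look better than it is.

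At stake is how the secondary results at 12 and 18 months are read: KOOS subscales, pain, EQ-5D-5L and MRI. The Abstract invites a comparison between arms at those visits. The body of the article neither specifies one nor rules it out, and the Limitations section mentions drop-out among controls but not this selection.

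**Working it through.** **Inputs from the plan.** SD 15, correlation between repeated measures 0.7, target difference 10, power 0.8, alpha 0.05, minimum N 44 rounded up to 60 (Sample size {14}); 1:1 allocation, so 30 per arm (Trial design {8}).

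**Inputs assumed.** The article gives neither a crossover rate nor its relation to outcome. I take crossover fractions f of 30, 50 and 70%. Controls with the lowest values of (9-month KOOS + independent decision noise) cross, with noise SD 0, 15 or 30. The correlation of 0.7 is applied between months 9 and 18.

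**1. The plan's own figure.** For change from baseline, SD = 15 × √(2 × (1 − 0.7)) = 11.62. Per arm, n = 2 × (1.96 + 0.842)² × 11.62² / 10² = 21.2, so 22, or 44 in total. The Hotelling-Lawley test of group by time over baseline, 3, 6 and 9 months, with differences 0, 10, 10, 10, also needs 44 (power 0.807). The stated size reproduces. It concerns only visits up to 9 months, before crossover is allowed.

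**2. Excess in the raw mean of the remaining controls at 18 months.**

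Excess = 15 × 0.7 × s × λ(f), where λ(f) = φ(z_f)/(1 − f), z_f is the f-quantile of the standard normal, and s = 15/√(15² + noise²) is the correlation of the crossover decision with the 9-month score.

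- λ(0.30) = 0.497, λ(0.50) = 0.798, λ(0.70) = 1.159.
- s = 1, 0.707 and 0.447 for noise SD 0, 15 and 30.
- Example: f = 50%, no noise: 10.5 × 1 × 0.798 = 8.4.

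| Crossover (assumed) | Controls left of 30 | Excess, noise 0 | Excess, noise 15 | Excess, noise 30 |
|---|---|---|---|---|
| 30% | 21 | 5.2 | 3.7 | 2.3 |
| 50% | 15 | 8.4 | 5.9 | 3.8 |
| 70% | 9 | 12.2 | 8.6 | 5.4 |

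Simulation agrees to within about 0.1 point. If crossover is unrelated to KOOS, the excess is zero.

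**3. Precision, before any bias.** Single-visit power for 10 points is Φ(10 / (15 × √(1/30 + 1/m)) − 1.96), with m controls. It is 0.73 for m = 30, 0.65 for 21, 0.56 for 15 and 0.42 for 9.

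**4. What a likelihood analysis would do.** In step 2, crossover depends only on the recorded 9-month score and pure noise, so the unobserved later control values are missing at random. Regressing the 18-month on the 9-month score among stayers, and predicting at the mean 9-month score of all controls, leaves a bias of at most about 0.1 point in all nine cells. A random-intercept mixed model with arm-by-visit terms (an assumption; section {20a} states no interaction) was also simulated: 30 per arm, six visits, the worst half of controls crossing and no true difference. Its 18-month estimate was 0.03 (simulation standard error 0.34), against −8.3 from raw means.

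**5. MRI.** The article gives no SD for T1rho, so no size is computed. The structure is the same: an 18-month scan timed from inclusion exists only for controls who stay on nonsurgical care. The stated t test is between time points and mixes time since inclusion with time since surgery. Both arms have a 6-month MRI, but no comparison between arms is stated for it.

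**The case against.** **The late comparison appears only in the Abstract.** The body limits the primary comparison to 9 months. Its only named KOOS analysis at 12 and 18 months is change from baseline in all IMPACT-treated patients, timed from treatment. This stands, and limits the point to a statement the visit schedule cannot support and the body leaves open for secondary outcomes. Handling of crossers may be detailed in a document not shown, but a stated comparison that conflicts with Table 1 is an inconsistency, not a missing detail.

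**The planned method is a mixed model, not raw means.** This also stands. A reader might infer that the planned analysis is biased by 2 to 12 points, or that it would hide or reverse a true benefit. The documents do not support that: under the mechanism that gives those figures, a likelihood model keeping the 9-month scores removes nearly all of the bias. The reassurance is conditional, however. It fails if crossover depends on symptoms or expectations that the recorded scores do not capture, which the data cannot test. Even where it holds, the model estimates what would have happened had nobody crossed over, from perhaps 9 to 21 controls.

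**The remaining outcomes are not all open-ended.** For nonsurgical care, the cost model uses EQ-5D-5L and costs from the first 9 months, so that input is untouched. For MRI, a reader might infer a biased 18-month test between arms; none is stated, since the t test compares time points.

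**Crossers could be analysed as randomised.** If surgery took place exactly at 9 months, their 3- and 9-month postoperative PROMs would fall at 12 and 18 months after inclusion. That avoids the selection but compares early with delayed IMPACT, not IMPACT with nonsurgical care.

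**Conclusion.** The point holds as a limited one. The Abstract states a comparison at 12 and 18 months after inclusion for which nonsurgical control data will exist only in patients who did not cross over. Because the plan regards crossover as treatment failure, these patients are probably selected on outcome, and a direct contrast would probably be biased against IMPACT.

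Under the plan's SD and correlation and an assumed crossover of 30 to 70%, the raw mean of the remaining controls would be about 2 to 12 KOOS points too high, against a target difference of 10. Direction is probable and size unknown, since neither the crossover rate nor its link to outcome is documented. The figures describe raw means, not a likelihood mixed model.

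A reader might infer that the main result is compromised. It is not: the primary intention-to-treat comparison ends at 9 months, when crossover first becomes possible, and the sample size of 44 reproduces for that window.

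**What to change.** - **Secondary PROMs (Outcomes {12} and Statistical methods {20a}):** state that IMPACT-versus-nonsurgical comparisons of KOOS subscales, pain and EQ-5D-5L end at 9 months after randomisation.
- **Data at 12 and 18 months:** present them as follow-up after IMPACT, as Outcomes {12} already does for KOOS, and separately as a description of controls who did not cross over, with the number remaining and no test against IMPACT.
- **MRI (Statistical methods {20a}):** compare 6-month T1rho between the randomised arms, adjusted for baseline, instead of only comparing time points by t test. Keep 18-month MRI descriptive.
- **Abstract:** align the sentence on visits with Objectives {7} and Outcomes {12}, separating the randomised comparison up to 9 months from later follow-up.

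This changes wording and one analysis of scans already scheduled; no visits or patients are added. The price is that no randomised claim for IMPACT over nonsurgical care can be made at 12 or 18 months, which the design does not support in any case.
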